### Screening

#### Depression

The CES-D [41] will be used as a screening instrument. It has been shown to be reliable and valid in studies across different populations, including students [55, 56].

#### Anxiety

The GAD-7 [42] will be used both as screening as well as outcome measure. It has been tested in students as well as different age groups and showed excellent reliability and validity [57, 58].

#### Demographic data, self-reported mental disorder diagnosis, and experience with psychotherapy

In addition to demographic data, such as age, participants indicate if they have ever received a diagnosis of any, and, if so, which, mental health disorder and whether they have ever utilized psychological treatment for any mental health condition.

#### Diagnostic interview

The M.I.N.I. [43] will be administered by telephone to establish DSM-V diagnoses of mood and anxiety disorders, bipolar disorder, psychosis, and the risk for suicide during screening. The reliability and validity of the M.I.N.I. has been established among several populations [59, 60].

### Primary outcome

The primary outcome is change in disorder-specific symptom severity from baseline to post intervention. For depression, this will be assessed using the QIDS-CR [44]. This interview has been used in different settings and has good psychometric properties [44, 61]. The SIGH-A [45] will be used for the assessment of anxiety. Its reliability and validity has been found to be good [45].

### Secondary outcomes

Secondary outcomes include self-reported reduction in depressive and anxiety symptoms from baseline to post intervention. In addition to screening, the GAD-7 will be used to measure anxiety symptoms throughout the trial. The nine-item Patient Health Questionnaire (PHQ-9; [62]) will be used to assess depressive symptoms. Research on the PHQ-9 has generally shown good psychometric properties among all age groups [62–64]. Moreover, the time to onset of a mood or anxiety disorder within the 12-month follow-up period will be assessed by the M.I.N.I. Finally, academic performance will be measured by the Presenteeism Scale for Students (PSS; [65]). It is a valid and reliable measure that will be used to assess presenteeism in the student population [65]. In addition, students will be asked to provide the number of points they acquired on the European Credit Transfer System (ECTS) during the semester.

### Costs

The CSRI [52] will be used to track societal costs. It has been adapted to the specifics of the Dutch college student context, measuring costs associated with healthcare use. In addition, it assesses absenteeism and presenteeism in college as well as in student jobs. For the latter, the Dutch minimum wage will be taken as an estimate of students’ income.

### Other outcomes, moderators, and mediators

#### Alcohol use

Alcohol use will be monitored by the three consumption questions of the brief Alcohol Use Disorders Identification Test (AUDIT-C; [66]). The AUDIT-C has shown good psychometric properties in college students [67]. Moreover, it has been used both as a screening as well as outcome instrument [68, 69].

#### Alliance (only intervention arms)

An adapted version of the self-rated Working Alliance Inventory (WAI-SR; [70]) will be administered to the active intervention groups. Questions relating to the bond with the coach will be asked only in the guided condition. The original form of the WAI-SR has shown good psychometric properties [70, 71].

#### Behavioral activation

The short form of the Behavioral Activation for Depression Scale (BADS-SF; [72, 73]) assesses activation and engagement in pleasant activities. The reliability and validity of the questionnaire has been established in a college student sample [74].

#### Dropout

Participants will be asked whether and why they have prematurely stopped using the intervention.

#### Expectations (only intervention arms)

The Credibility/Expectancy Questionnaire (CEQ; [75]) will be used to assess participants’ expectations of the intervention. Its reliability and validity has been established and the questionnaire has been used in college student samples [75, 76].

#### Incongruence

ICare Prevent aims at reducing the gap between motivational goals and their actual execution. The short version of the incongruence questionnaire (INKK; [77]) measures the extent to which this is achieved.

#### Motivation

The Treatment Entry Questionnaire (TEQ; [78]) will be used to assess motivation to participate in the study. Research has indicated good psychometric properties for the TEQ in a Dutch psychiatric sample [79].

#### Negative effects of the intervention (only in intervention arms)

The Inventory for the Assessment of Negative Effects of Psychotherapy (INEP; [80]) measures possible negative aspects of using the intervention.

#### Personality

The ten-item Big Five Inventory (BFI-10; [81, 82]) will be used as a brief measure of personality. Its psychometric properties have been established in a college student sample [82].

#### Potential risk factors

Participants can choose if they want to answer a battery of potential risk factors for mental wellbeing that have been suggested by the literature, such as smoking, body image, and childhood abuse.

#### Program evaluation (only in intervention arms)

The eight-item Client Satisfaction Questionnaire has been adapted to this online context (CSQ-8; [83, 84]). It assesses participants’ satisfaction with the intervention. The psychometric properties of the Dutch version have been found to be good [85].

#### Quality of life

In addition to the Assessment of Quality of Life questionnaire (AQoL-8D; [86, 87]), the EuroQol (EQ-5D-5 L; [88]) will be administered. This enables the calculation of quality-adjusted life-years (QALYs) and converting health states into utility scores using the Dutch EQ-5D-5 L tariff [89]. Both instruments have established psychometric properties [86, 90].

#### Resilience

The ten-item version of the Connor-Davidson Resilience Scale (CD-RISC; [91]) measures how good individuals can work under pressure or how strong they think they are. The CD-RISC has been used in college samples and its reliability and validity has been well established in different populations [92–94].

#### Sleep quality

One item on sleep quality from the Pittsburgh Sleep Quality Index (PSQI; [95]) will be administered. The PSQI has been used extensively in college samples [96, 97].

#### Support (only in guided intervention arm)

Seven items have been developed by the research team to assess the relationship between participants and their eCoach (e.g. “I think my eCoach appreciates me less if I use ICare Prevent less often than expected”), as well as how they would rate the eCoach’s competency (e.g. “I think my eCoach is very competent”).

#### Wellbeing

Wellbeing will be measured by the five-item version of the World Health Organization Ten Well-Being Index (WHO-5; [98]). Good psychometric properties of this instrument have been established in a college and Dutch population [99, 100].

#### Worry

The ultra-brief version of the Penn State Worry Questionnaire (PSWQ-3; [101]) has good psychometric properties and will be administered to examine excessive worrying [101, 102].

### Sample size calculation

The primary endpoint is change in disorder specific symptom severity from baseline to post intervention. Based on the evidence from a meta-analysis by Cuijpers et al. [103] on the effectiveness of psychotherapies for subclinical symptoms of depression, as well as a randomized controlled trial on the effectiveness of an Internet-based intervention for subclinical depression ([24–26], the expected effect size is *d* = 0.35. Due to a lack of information on effect sizes for subclinical symptoms of anxiety, *d* = 0.25 is used as a conservative estimation for both conditions. A study comparing the effectiveness of Internet-based psychotherapy with different levels of support found effect sizes in a similar range [39]. The sample size calculation is based on a repeated measure ANOVA and follows the recommendations given in Muller [104] and Muller et al. [105]. Thus, based on a global significance level α = 0.05 and power β = 0.95, 252 participants (84 per study arm) will be needed for an effect of 0.25 to be significant.

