**Methods:**

A three-arm, parallel, randomized controlled superiority trial will be conducted comparing a guided and an unguided version of ICare Prevent with a control group receiving CAU. The trial will be open-label but outcome assessors will be blinded. A total of 252 college students (age ≥ 16 years) with subclinical symptoms of depression defined as a score ≥ 16 on the Center for Epidemiological Studies Depression Scale (CES-D), and/or anxiety, defined as a score ≥ 5 on the Generalized Anxiety Disorder scale (GAD-7), will be included. Those meeting diagnostic criteria for a depressive or anxiety disorder will be excluded. The primary outcome is change in disorder specific symptom severity from baseline to post-intervention. Secondary endpoints include self-reported depression and anxiety symptoms as well as time to onset of a mood or anxiety disorder until 12-month follow-up. Societal costs and quality of life will be assessed to estimate the intervention’s cost-effectiveness compared to CAU.

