### Randomization, treatment allocation, and blinding

The allocation scheme will be derived by computer using a random number generator at a 1:1:1 ratio. Participants will be randomized at an individual level by an independent institute (University of Münster, Germany) and randomization will be stratified by type of subclinical symptoms (depression or anxiety). Due to the nature of the study it is not possible to blind either participants or coaches, as they will be notified to which of the three conditions they have been assigned to. However, raters who perform the clinical interviews to assess outcomes will be blinded. In order to ensure that blinding was successful, participants will be informed about the importance not to indicate their allocation status at the beginning of the telephone interviews. Moreover, raters will be asked to guess the allocation status of each participant after the second interview at post intervention. The results will then be compared to what would have been expected by chance. The flowchart of the trial is shown in Fig. 1.

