### Statistical analysis

All analyses for the primary and secondary outcomes will be based on multilevel mixed model regression analyses for continuous outcomes in order to assess change over time. Time will be used as a predictor variable and baseline measures will be included as covariates. Linear models will be used for normally distributed data and negative binomial models for left-skewed data. All analyses will be performed on an intention-to-treat (ITT) sample. Per-protocol analyses including only participants who conformed to their group allocation will be performed in addition. Missing data will be handled using either multiple regression imputation techniques if appropriate or full information maximum likelihood estimation [106]. The secondary outcome, time to mental health disorder onset during 12 months follow-up in all conditions, measured by the M.I.N.I., will also be compared using survival curve analysis. The curves will be compared using cox proportional hazard regression analysis using baseline symptom severity as a covariate. Hazard ratios will be calculated as measure of the effect size of group differences. Within secondary analyses, interactions with predictors will be added to the model in order to identify risk and protective factors.

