### Strengths and limitations

To our knowledge, this is the first trial that investigates the (cost-)effectiveness of a transdiagnostic individually tailored Internet-based intervention for the prevention of depression and anxiety in a college student population. Data on both symptom reduction as well as the time to onset of a mood or anxiety disorder will be measured. Although some research suggests that Internet-based interventions have the potential to be cost-effective compared to no treatment, no data are available for preventive transdiagnostic individually tailored Internet-based interventions for college students. Specifically, the added (economic) value of support by means of an eCoach needs to be closely monitored in the context of this low-intensity intervention.

Some possible limitations of the present trial should be noted. First, the sample size of this trial conducted among Dutch college students is insufficient for directly comparing the guided and unguided treatment arm as well as analyzing the time to a mental health disorder onset. Similarly, analyses of moderators and mediators will be underpowered and may therefore provide only limited insights. To counter this issue, data from all participating trials in the ICare project will be pooled in order to achieve enough statistical power. Second, an evaluation of societal costs might be difficult due to the fact that most students are seldom in full-time employment. The detrimental effect of depression and anxiety on absenteeism and presenteeism in the context of employment is therefore difficult to quantify. In order to increase the validity of the results, we have adapted the cost-effectiveness questionnaire (CSRI; [52]) to fit the specifics of a student population by focusing on absenteeism and presenteeism in student jobs, as well as in lectures. Finally, previous research has shown that adherence to Internet interventions is a point of concern, especially in unguided formats [111, 112]. A series of automatic motivational messages and reminders will be used in order to increase adherence in the unguided study arm and we will closely observe factors related to dropout. This will be beneficial in designing future interventions and improving uptake of intervention content.

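### The 252 students to be included equal the complete-data minimum for the stated 95% power, so the figure appears to hold no allowance for missing post-intervention interviews

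*Protocol article*

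**What the plan says.** The section Sample size calculation sets its targets as "based on a global significance level α = 0.05 and power β = 0.95" (read here as power 0.95). It names its method: "The sample size calculation is based on a repeated measure ANOVA". It takes an effect of 0.25, which "is used as a conservative estimation for both conditions", and concludes that "252 participants (84 per study arm) will be needed for an effect of 0.25 to be significant". It mentions no attrition rate and no inflation, and it gives neither the number of time points nor the within-person correlation.

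The abstract, under Methods, gives the same figure as the number to be included: "A total of 252 college students (age ≥ 16 years) with subclinical symptoms of depression". Allocation is 1:1:1, so 252 means 84 randomised per arm.

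The section Statistical analysis provides for incomplete outcomes: "Missing data will be handled using either multiple regression imputation techniques if appropriate or full information maximum likelihood estimation". In Table 3 the two primary instruments, QIDS-CR and SIGH-A, are scheduled at T0 (screening), T3 (post intervention), T4 and T5, and not at T1 or T2. The primary outcome is change from baseline to post intervention.

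**The concern.** The number the calculation needs and the number the trial includes are the same. A power calculation of this kind counts people whose outcome is observed, whereas the abstract counts people who enter. The two agree only if every T3 interview takes place, and the analysis section makes provision for the case where some do not.

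The measurement schedule makes this more than a formality. T3 is the first time after randomisation that the primary scales are taken. A student who misses T3 and does not return has no post-randomisation QIDS-CR or SIGH-A value, so in a likelihood analysis of those scales alone adds essentially nothing to the T3 contrast.

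At stake is how the result is read. Someone who takes 95% at face value will treat a null finding as stronger evidence against an effect of 0.25 than the trial can give.

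**Working it through.** **Inputs.** From the article: three arms at 1:1:1, α = 0.05, power 0.95, effect 0.25, N = 252. Assumed, because the article does not state them: two time points and within-person correlation r = 0.5 for the repeated-measures reading, and T3 loss of 10%, 20% and 30%.

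**Step 1: reproduce 252 with complete data.** Power is the probability that a noncentral F variable with 2 and N − 3 degrees of freedom and noncentrality λ exceeds the 5% critical value.

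- Reading A, one-way three-group F with f = 0.25: λ = N × f². At N = 252, λ = 252 × 0.0625 = 15.75.
- Reading B, group-by-time interaction with m = 2 time points and f = d/2 = 0.125: λ = N × f² × m/(1 − r). At N = 252 and r = 0.5, λ = 252 × 0.015625 × 2/0.5 = 15.75, with the same degrees of freedom.

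The two readings therefore give identical power:

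| N observed | λ | Power |
|---|---|---|
| 249 (83 per arm) | 15.56 | 0.9491 |
| 251 | 15.69 | 0.9507 |
| 252 (84 per arm) | 15.75 | 0.9515 |

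The smallest balanced total reaching 0.95 is 252, the article's own figure. The match needs no dropout term and leaves no room for one.

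**Step 2: dependence on the unstated correlation.** Under reading B the balanced minimum is 351 at r = 0.3, 252 at r = 0.5, 201 at r = 0.6 and 153 at r = 0.7. Only r = 0.5 among these gives 252. Had the authors assumed r = 0.6, then 252 would leave 252 − 201 = 51 students, or 51/252 = 20%, to spare.

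**Step 3: effect of T3 loss.** Keep the formula of step 1 and let students without a T3 interview contribute nothing. Analysed N is 252 × (1 − loss), rounded down:

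| Assumed T3 loss | Analysed N | λ = N × 0.0625 | Power | Shortfall from 95% |
|---|---|---|---|---|
| 10% | 226 | 14.13 | 92.7% | 2.3 points |
| 20% | 201 | 12.56 | 89.3% | 5.7 points |
| 30% | 176 | 11.00 | 84.6% | 10.4 points |

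Power first drops below 80% at a balanced 156 analysed, a loss of (252 − 156)/252 = 38%.

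**The case against.** **Dropout in this article is not loss of outcomes.** The limitations section says that "previous research has shown that adherence to Internet interventions is a point of concern, especially in unguided formats", and a reader might infer that the authors themselves expect T3 interviews to be missing. The text does not support that. The passage concerns use of the programme, and the Dropout measure asks whether and why someone stopped using the intervention. The T3 assessment falls at eight weeks or at post intervention, whichever comes first, so a student who abandons the modules can still be interviewed and is analysed by intention to treat. This objection stands. The support for missing outcomes is the missing-data sentence in Statistical analysis, which names no expected level.

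**The loss is gradual.** A reader might also infer that one missing interview defeats the stated power. It does not: 251 observed still give 0.9507.

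**The correlation is inferred.** Step 2 shows that a higher assumed correlation would leave slack. This stands as a limit. Against it, 252 is hit exactly by two simple readings, and the article presents 252 as the number needed.

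**Some information is recoverable.** PHQ-9 and GAD-7 are taken at T2 and T3, and the primary interviews again at T4 and T5. Imputation or full-information likelihood can use these, so step 3 is pessimistic. They cannot be expected to restore full complete-data power.

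**The planning effect is conservative.** The article expects d = 0.35 for depression. Scaling the effect to 0.35 in the same formula gives power 0.996, 0.989 and 0.975 at 20%, 30% and 40% loss. But the stated 95% is for 0.25, and the article says it lacks effect-size information for anxiety, so no such margin can be claimed there.

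**A condensed article may leave attrition to the full protocol.** Silence alone would be no finding. The point rests on the published number coinciding with the uninflated minimum.

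**Conclusion.** The point holds in a limited form. The 252 students to be included match the complete-data requirement, so the stated 95% appears to describe a trial in which every T3 interview is obtained. Under the formula that reproduces 252, assumed T3 losses of 10%, 20% and 30% give power of about 92.7%, 89.3% and 84.6%. These figures rest on three assumptions: the loss rates, which the article does not give; r = 0.5 or its one-way equivalent; and no information from students without a T3 interview. The last makes them lower bounds for the formula and loss in question.

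No arithmetic in the article is wrong on this point, and under this formula power stays above 80% until about 38% are missing. What needs correcting is the stated power, not the design. The formula also carries an unresolved question of scale: 0.25 is called d in the article, yet reading A reproduces 252 only by treating it as f. That is a separate matter, and the percentages here should not be taken as the trial's true power for an effect of d = 0.25.

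**What to change.** In Sample size calculation:

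1. Say that 252 (84 per arm) is the number needed with a T3 QIDS-CR/SIGH-A interview and, if that is so, that it includes no allowance for missing interviews.
2. State the number of time points and the within-person correlation used. If a correlation above 0.5 was assumed and 252 does include an allowance, say so and give its size.
3. State the expected T3 loss with its basis, and replace 95% with the power for 252 randomised at that loss. Calculate it after settling whether 0.25 is d or f. A short table at 10%, 20% and 30% loss would do.

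This costs a few sentences and a short rerun. It requires no extra enrolment and no change to design or analysis. The only downside is a less favourable stated power.

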### Statistical analysis

All analyses for the primary and secondary outcomes will be based on multilevel mixed model regression analyses for continuous outcomes in order to assess change over time. Time will be used as a predictor variable and baseline measures will be included as covariates. Linear models will be used for normally distributed data and negative binomial models for left-skewed data. All analyses will be performed on an intention-to-treat (ITT) sample. Per-protocol analyses including only participants who conformed to their group allocation will be performed in addition. Missing data will be handled using either multiple regression imputation techniques if appropriate or full information maximum likelihood estimation [106]. The secondary outcome, time to mental health disorder onset during 12 months follow-up in all conditions, measured by the M.I.N.I., will also be compared using survival curve analysis. The curves will be compared using cox proportional hazard regression analysis using baseline symptom severity as a covariate. Hazard ratios will be calculated as measure of the effect size of group differences. Within secondary analyses, interactions with predictors will be added to the model in order to identify risk and protective factors.

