Choice module	Topic
1	Sleep
2	Perfectionism
3	Gratitude
4	Self-esteem
5	Alcohol consumption (includes AUDIT-C)
6	Relaxation
7	Acceptance
8	Rumination
Diary	Topic
1	Positive activities
2	Negative thoughts
3	Sleep
4	Challenging situations
5	Alcohol consumption

The intervention can be used on (laptop) computers, mobile phones, and tablets. The mobile app can be used optionally. It provides access to the diaries and allows participants to activate push notifications. These short messages contain small exercises, such as short relaxation techniques, as well as motivational texts. The intervention uses a responsive web design in order to tailor content to participants’ needs, based on the choices they make. An optional read-aloud function is included. The expected time to complete each session is approximately 60 min. The two intervention conditions only differ in the support participants receive. In the guided condition, trained eCoaches (clinical psychology master students) spend approximately 20 min, but no more than 30 min per session on sending individual manualized feedback on the exercises through the intervention platform. In addition, they will send reminders for module completion in order to increase adherence. The eCoaches will be supervised by the members of the research team. Participants in the unguided condition receive only automatic motivational messages that aim to increase adherence by positively reinforcing participants for completing intervention modules and reminding them in case of a delay in completion.

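### Only guided-arm students are nested within eCoaches, and neither the sample size nor the stated primary model allows for it; if coaches differ, the guided-versus-CAU standard error is too small

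*Protocol article*

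**What the plan says.** All places are in the protocol article; a separate statistical analysis plan is not shown.

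- **Unit of randomization** (Randomization, treatment allocation, and blinding): "Participants will be randomized at an individual level by an independent institute". The ratio is 1:1:1, and the only stratification factor is type of subclinical symptoms.
- **Who delivers support** (Intervention): "In the guided condition, trained eCoaches (clinical psychology master students) spend approximately 20 min, but no more than 30 min per session". This time goes to manualized feedback; the coaches also send reminders, and the research team supervises them. The unguided arm gets automatic messages only, and support is the sole difference between the two active arms.
- **Link between student and coach** (Support): guided-arm items "assess the relationship between participants and their eCoach", which implies that each guided student has an identifiable coach.
- **Sample size** (Sample size calculation): "The sample size calculation is based on a repeated measure ANOVA". The inputs are a global significance level of 0.05, power of 0.95 and an effect of 0.25, giving 84 per arm. No ICC, caseload or design effect appears.
- **Model** (Statistical analysis): the primary and secondary outcomes are to be analysed by "multilevel mixed model regression analyses for continuous outcomes in order to assess change over time. Time will be used as a predictor variable". Baseline enters as a covariate. The levels of the model are not listed.
- **Guided versus unguided** (Strengths and limitations): the trial is said to be too small for this comparison, and pooling with the other ICare trials is planned.

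**The concern.** Several guided students will normally share a coach. If some coaches obtain better results than others, outcomes of students with the same coach are correlated, and 84 guided students carry less information than 84 independent ones. Students in the unguided and CAU arms have no such grouping. This is a partially nested design.

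The one structure that the analysis text describes is change over time, that is, repeated measurements within a student. A model with that structure alone would understate the standard error of the guided-arm mean. The guided-versus-CAU test on QIDS-CR and SIGH-A would then reject too often, while unguided versus CAU would keep its nominal error rate. The distortion would favour one of the two active arms, in a trial that asks what eCoach support adds.

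**Working it through.** **1. Does the stated sample size contain any allowance for coaches?** Take a repeated-measures ANOVA, group-by-time interaction, 3 groups, 2 time points, f = d/2 = 0.125. The correlation between time points is not stated; assume 0.5.

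Noncentrality = N × f² × 2/(1 − 0.5) = 252 × 0.015625 × 4 = 15.75, with 2 and 249 degrees of freedom.

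Power is 0.951 at N = 252 and 0.949 at N = 249, so 252 is the smallest balanced total that reaches 0.95. The figure reproduces with independent participants and no design effect.

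**2. Effect of clustering in one arm.** Let k be the number of coaches and m = 84/k the caseload.

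- Design effect in the guided arm: DE = 1 + (m − 1) × ICC
- True over naive standard error, guided versus CAU: r = √((1 + DE)/2)
- Actual type I error of a nominal two-sided 5% test: 2 × (1 − Φ(1.96/r))

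Both k and the ICC are assumptions. Worked case, ICC 0.05 and k = 8: m = 10.5; DE = 1 + 9.5 × 0.05 = 1.475; effective guided n = 84/1.475 ≈ 57; r = √(2.475/2) = 1.112; 1.96/1.112 = 1.76; type I error 7.8%.

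| ICC | Coaches | DE | SE ratio | Type I error |
|---|---|---|---|---|
| 0.01 | 4 | 1.20 | 1.049 | 6.2% |
| 0.01 | 8 | 1.095 | 1.023 | 5.6% |
| 0.01 | 20 | 1.032 | 1.008 | 5.2% |
| 0.05 | 4 | 2.00 | 1.225 | 11.0% |
| 0.05 | 8 | 1.475 | 1.112 | 7.8% |
| 0.05 | 20 | 1.16 | 1.039 | 5.9% |
| 0.10 | 4 | 3.00 | 1.414 | 16.6% |
| 0.10 | 8 | 1.95 | 1.214 | 10.7% |
| 0.10 | 20 | 1.32 | 1.077 | 6.9% |

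Simulating a single-outcome version of the contrast (84 guided students spread over k coaches, 84 independent controls, naive t test) agrees. At ICC 0.05 it gives about 11%, 7.8% and 5.8% for 4, 8 and 20 coaches.

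**3. Effect on power.** If both active arms differ equally from CAU, the noncentrality behind 252 corresponds to a difference of 0.25 × 3/√2 = 0.53 SD of change. Guided-versus-CAU power is 0.930 under independence. It becomes 0.871 at ICC 0.05 with 8 coaches, 0.926 at ICC 0.01 with 20 coaches, and 0.681 at ICC 0.10 with 4 coaches. Omnibus power moves less: 0.951 to 0.938 in the middle case. These figures use a normal approximation, so the further loss from few degrees of freedom is not included; it matters when there are only a few coaches.

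**4. Does the remedy hold its error rate?** The same simulation was run with a coach-mean test and Satterthwaite degrees of freedom, reverting to the naive test whenever the coach variance is estimated at zero or below. The type I error stays at about 4% to 6% for ICC 0.01 to 0.10 and 4, 8 or 20 coaches.

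**The case against.** **The model is called multilevel and its levels are not listed.** This stands. A reader might infer that the primary model treats all participants as independent. The text does not say so: it neither includes nor excludes a coach effect, and a separate analysis plan could add one. What can be said is that the article names the model's purpose and terms and leaves out the one grouping that its own design creates. For the sample size no such doubt arises, because the figure reproduces under independence.

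**The size rests on two assumed numbers.** This stands too. Feedback is manualized, limited in time, and given by supervised coaches of the same training background, which points to a low ICC. At ICC 0.01 the error rate is only 5.2% to 6.2%. The Support items record students' perception of their coach and are not evidence that coaches differ.

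**Guided versus unguided is already conceded.** The article calls the trial too small for that comparison, so the consequence here falls on guided versus CAU. Pooling does not remove the issue, since the design effect depends on caseload and not on total N.

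**A coach variance estimated at zero brings the naive test back.** This happens often: in about 28% to 32% of simulated trials at ICC 0.05 and about half at ICC 0.01. Even so, the overall error rate stays at about 4% to 6%, so the objection fails.

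**Conclusion.** The point holds in conditional form. Guided students are nested in eCoaches, the sample size assumes independence, and the analysis section specifies no eCoach level. If outcomes vary between coaches and no such level is added, the guided-versus-CAU standard error is too small. Under an assumed ICC of 0.01 to 0.10 and 4 to 20 coaches it is understated by a factor of about 1.01 to 1.41, and the type I error is about 5% to 17% (about 8% at ICC 0.05 with 8 coaches). The lower end is the more plausible given manualized, supervised feedback, and with many coaches or an ICC near zero nothing of consequence remains.

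Two stronger readings are not supported. One is that the reported standard errors will be too small as a matter of fact: the article gives neither the ICC nor the number of coaches. The other is that both active arms are affected: unguided versus CAU has no coach grouping and keeps its nominal properties.

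**What to change.** In the Statistical analysis section, state that contrasts involving the guided arm use a partially nested mixed model: a random eCoach effect for guided participants only, absent in the unguided and CAU arms, with Satterthwaite or Kenward-Roger degrees of freedom. The minimum is to prespecify this as a sensitivity analysis.

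Keep the eCoach identifier for each guided participant, and carry it into the pooled ICare analysis. Report the number of eCoaches, the caseload and the estimated ICC.

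The cost is about one sentence and one variance term. Feedback already passes through the intervention platform, so no new visits or questionnaires should be needed, and no extra enrolment is required. The price is a wider interval and lower power for guided versus CAU, marked if there are only a few coaches and slight otherwise.
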